#### ***Recruiting and interviewing young people***

Young people were recruited into the trial in the ‘baseline profile’ and the ‘post-intervention’ phase (see Figure 2). The ‘baseline profile’ was collected prior to the randomisation of the practices to provide a snapshot of the young people seen by the clinician and to assess for baseline differences between the study arms after randomisation. The post-intervention sample of young people was a different sample from the baseline sample and became the study cohort followed up at 3 and 12 months.

a) Inclusion/exclusion criteria

All youth aged 14–24 years attending participating clinicians were eligible for participation. Exclusion criteria were: being physically or mentally (very) unwell (vomiting, febrile, weak, cognitively impaired or psychotic); unable to read or speak English; being under 18 years of age AND unable or unwilling to obtain parental consent AND judged by the clinician as incompetent to make an informed decision for participation in minimal risk research (that is, an immature minor) [61].

b) Recruitment and interview

Recruitment of young people into the study occurred in two phases. First, clinicians were trained to ask all eligible young people, after their consultation had finished, whether they would be willing for their contact phone number to be passed on to researchers for a full explanation of the study. GPs or PNs recorded telephone numbers of interested youth and any reasons for refusal or ineligibility; the clinicians were asked to fax this list to the researchers daily. The computer assisted telephone interview (CATI) staff telephoned all listed youth (usually on the same day) to fully explain the study and obtain formal consent. CATI staff then conducted the exit interview with consenting young people or made an appointment for the interview to take place at a time convenient for the young person. The interview (approximately 50 minutes long) could also be completed over several phone calls if not finished in one sitting. Young people were first notified by Short Messaging Service (SMS) to alert them that a call was coming from the project team. At the end of the interview, CATI staff obtained consent to telephone young people for the three month and 12 month follow-up periods. Follow-up interviews were approximately 20 minutes long. Young people had up to 20 telephone call attempts for up to two weeks before they were recorded as a missed recruit.

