#### ***Post-intervention sampling of young people and parents***

Eight weeks after randomisation and six weeks after the practice staff completed the intervention, practices recruited the young patients who formed the cohort followed up at three months and 12 months post-consultation. Clinicians were again instructed to recruit all eligible young people aged 14–24 years with whom they consulted until the required sample size for each practice was achieved. Parents attending with young people under the age of 18 years were instructed to complete the written parent survey and return it to researchers in a reply paid envelope. Clinicians again completed a clinician encounter form on each youth consult.

Our monitoring of recruitment rates of young people revealed that clinicians were failing to recruit continuously, and systematically; the timeframe for recruitment extended over long periods that varied from 13 days to nearly 11 months (mean 86.3 days). Within the longer periods, recruitment was inconsistent, influenced by practice constraints (e.g., accreditation activities, staff absence including extended sick leave as was the case for the practice which took 11 months). To complete the study within a reasonable timeframe and to ensure that all eligible young people were approached and recruited into the study, we changed our recruitment strategy for the last 15 practices by placing a research assistant in the waiting room to systematically approach every young person with an invitation to be involved. Slightly more intervention practices (8/19 intervention versus 7/21 comparison practices) received this assistance because recruitment in the intervention practices was delayed after randomisation due to longer times taken for training clinicians compared to the comparison practices. The additional benefit of the in-practice research assistants was the timely, daily transfer of phone numbers of eligible young people to the CATI interviewers and accurate recording of reasons for refusal to participate or ineligibility.

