### **Data analysis plan**

Quantitative outcomes: Descriptive statistics will be used to compare clinician and young person’s characteristics between the two study arms at baseline and measures taken immediately after the consultation. Intra-cluster correlation will be reported for the main outcomes. Analysis will be by intention to treat and results will be reported following the extended consort statement for cluster randomised trials [58]. Marginal linear and logistic regression models using generalised estimating equations with robust standard errors will be used to adjust for the clustering effect of randomising the general practices and outcomes measured at the young person’s level. Marginal logistic regression will be used to estimate the intervention effect for binary outcomes and will be reported as odds ratios. Marginal linear regression will be used to estimate the intervention effect for continuous outcomes and will be reported as the difference in the mean outcome between the two study arms. Estimates of the intervention effect will be reported with their respective 95% confidence intervals and p-values. Multivariable regression models will be used to adjust for variables used to stratify randomisation (SES of the practice location, practice billing type) and for imbalanced baseline factors identified a priori to be strongly associated with the outcome, namely the baseline risk factor status of young people and prior training in adolescent health. Recruitment method of young people in the trial will also be adjusted for in the regression model (clinician versus research assistant).

Qualitative outcomes: Interviews with practice staff on acceptance of screening processes will be transcribed and analysed for themes. Secondary outcomes of pathways to care (health service use) [65] will be described and parental attitudes will be summarised for each arm.

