As expected when conducting a trial in the real world setting, some changes to the protocol after trial registration, were necessary to overcome practical constraints in conducting the trial. These constraints arose because of the sheer busyness of general practice which prevented staff from adhering to some of the original research protocol, as well as the lack of functionality in practice software to enable accurate, easy collection of data on the number of presenting patients in each practice per day [72].

There is a possibility that unsystematic clinician recruitment could have introduced a recruitment bias, although this problem would occur in both arms of the trial. There is also a possibility of systematic bias or differential recruitment [73] in the two study arms because young people were recruited after practices were randomised and were therefore approached by clinicians who knew their study arm status. It was not possible to recruit patients prior to randomisation of practices because the intervention being tested was opportunistic screening for, and response to, health risks for a young person presenting for any reason to their clinician on the day. In addition, the alternative of RAs recruiting patients instead of the clinicians carried prohibitive costs when we started this trial. We tried to circumvent this risk of differential recruitment by asking clinicians to record information on all young people seen and by having CATI staff (blinded to study arm status) actually obtain the consent and conduct the interviews. The change in recruitment strategy to in-practice RAs, three quarters into the trial, will be adjusted for in our final analyses as the type of young people recruited by each method may be different.

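### The stated covariate list omits the young person's own age and sex, although the analysed cohort was recruited after practices were randomised and randomisation does not ensure its balance

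*Protocol article*

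**What the plan says.** The Data analysis plan names its adjustment variables in three groups.

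- Practice-level stratifiers. The models will "adjust for variables used to stratify randomisation (SES of the practice location, practice billing type").
- Imbalanced baseline factors chosen a priori for a strong association with outcome, "namely the baseline risk factor status of young people and prior training in adolescent health".
- Recruitment method. "Recruitment method of young people in the trial will also be adjusted for in the regression model (clinician versus research assistant").

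The young person's age and sex appear in none of these groups. The same section says that young people's characteristics will be compared between arms with descriptive statistics, without saying which ones.

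On how the cohort was formed, the section on post-intervention sampling says: "Eight weeks after randomisation and six weeks after the practice staff completed the intervention, practices recruited the young patients who formed the cohort". The section on recruiting and interviewing says: "The post-intervention sample of young people was a different sample from the baseline sample and became the study cohort followed up at 3 and 12", where the two numbers are the follow-up times in months. The Discussion accepts that differential recruitment is possible, because "young people were recruited after practices were randomised and were therefore approached by clinicians who knew their study arm status".

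Eligibility covers ages 14 to 24. A person under 18 without parental consent is excluded if also "judged by the clinician as incompetent to make an informed decision for participation in minimal risk research".

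**The concern.** In this design the practices are randomised, but the young people enter later. The usual argument that any difference in age or sex between arms is only chance is therefore not available. A difference can also arise from whom clinicians approach, and the protocol reports that clinician recruitment was neither continuous nor systematic. The competence judgement on minors adds a narrow route that bears on age directly.

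The Background says that risky behaviours emerge in these years, so some age gradient across 14 to 24 is to be expected. If the arms differ in age mix and the model has no age term, part of that gradient appears in the intervention estimate, as a false effect or a masked one. This applies to detection, alcohol, drugs, tobacco and distress. Age and sex cannot be changed by the intervention, so entering them carries no risk of adjusting away a real effect.

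**Working it through.** **1. The plan's own figures.** The Sample size estimation section gives ICC 0.04 and 18 young people per practice in 40 practices.

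- VIF = 1 + (18 − 1) × 0.04 = 1.68, as stated.
- For 24% v 36.5%, two-sided 5% and 80% power, 211 per arm are needed. 211 × 2 × 1.68 = 709, against 720 stated (18 × 40).
- Allowing for 40% loss: 18 / 0.6 = 30 per practice.

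These figures reproduce, and nothing below changes them.

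**2. Who recruited.** "Slightly more intervention practices (8/19 intervention versus 7/21 comparison practices) received this assistance". So 15 of 40 practices had research assistants, who are described under Blinding as blind to arm. Clinicians who knew their arm recruited in the other 25: 19 − 8 = 11 intervention and 21 − 7 = 14 comparison.

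**3. Standard error.** With 360 per arm, VIF 1.68 and the 41% alcohol prevalence of Table 2:

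SE = √(2 × 0.41 × 0.59 × 1.68 / 360) = 0.0475, or about 4.8 points.

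**4. Bias with no age term and no baseline risk term.** Bias = difference in age mix × difference in prevalence between age groups. The protocol gives neither input, so both are assumed. With b the bias, the rejection rate under a true null is 1 − Φ(1.96 − b/SE) + Φ(−1.96 − b/SE).

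| Arm difference in share aged 18–24 | Bias, 25% v 50% | Rejection rate | Bias, 15% v 30% |
|---|---|---|---|
| 5 points | 1.25 | 5.8% | 0.75 |
| 10 points | 2.5 | 8.2% | 1.5 |
| 15 points | 3.75 | 12.4% | 2.25 |

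These rates apply to a systematic difference in age mix. Chance imbalance is already reflected in the standard error. For scale, the SD of chance imbalance in a 50% characteristic, if it also has ICC 0.04, is √(2 × 0.25 × 1.68 / 360) = 4.8 points.

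**5. What baseline risk status would absorb.** A simulation with no intervention effect used prevalence 41%, age gaps of 10 to 30 points and age imbalances of 10 to 20 points. Each person's follow-up status either repeated their baseline status (probability 0.5 or 0.7) or was redrawn from the age-specific prevalence. Estimated bias in points:

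| Imbalance, gap, stability | No adjustment | Own baseline risk | Own baseline risk + age group |
|---|---|---|---|
| 10, 20, 0.5 | 1.78 | 0.75 | −0.20 |
| 10, 30, 0.5 | 3.13 | 1.53 | 0.18 |
| 20, 30, 0.5 | 6.18 | 2.98 | 0.20 |
| 20, 30, 0.7 | 6.07 | 1.52 | −0.10 |

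Across all settings, adjusting for a person's own baseline status left about 0.1 to 3 points, half of the unadjusted bias or less. Adding age group brought it to about zero, within simulation error. Halving the 2.5-point case in step 4 gives 1.25 points and a rejection rate of 5.8%.

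**6. Whether the plan has that covariate.** In this article, baseline usually means the separate sample taken before randomisation. The Data analysis plan itself sets baseline apart from measures taken immediately after the consultation. Read that way, baseline risk status is only a practice-level summary, and no personal characteristic of a cohort member is adjusted for. Read as status at the exit interview, it is individual and absorbs much of an age imbalance. The text does not decide. Even on the second reading, it does nothing for uptake of a behaviour among those without it at entry, because their baseline status is constant.

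**7. Precision.** With equal age groups, age would explain 0.25 × 0.25² / (0.375 × 0.625) = 6.7% of the variance for 25% v 50%, and 0.25 × 0.15² / (0.225 × 0.775) = 3.2% for 15% v 30%. Any gain is modest.

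**The case against.** The strongest reply is that this is a condensed article, that a separate analysis plan may name more covariates, and that asking for two more is a preference. The first two points are true. But the article does not leave the subject open: it states the list and closes the prognostic part with two named factors. A comment on a stated list is not a complaint about missing detail.

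The reply on size is stronger, and most of it stands:

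- No age split, prevalence by age or expected arm difference is given, so every bias figure above is hypothetical.
- The planned adjustment for baseline risk status may already absorb half or more of an age imbalance.
- In 15 practices, research assistants blind to arm approached every young person. Elsewhere clinicians were asked to record everyone seen, blinded telephone interviewers obtained consent and interviewed, and recruitment method is adjusted for. That last term does not correct an arm difference in age within the clinician-recruited practices.
- The exclusion of minors needs three conditions together, so it could hardly shift the age mix of the whole cohort by 10 to 15 points on its own.
- Table 1 lists demographic items for staff only, so recording of the young person's sex is an inference.

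A reader might infer that age and sex are the strongest predictors of risk behaviour. The protocol does not say so. The factors it calls strongly associated with outcome are baseline risk status and prior training. It supports an age gradient in general terms, and nothing in it ranks sex as a predictor.

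**Conclusion.** The point holds as a gap in a stated adjustment set: two plausible predictors, fixed before the intervention, are left out of models for a cohort whose individual-level balance randomisation does not ensure. Before adjustment for baseline risk status, the bias is about 1.3 to 3.8 points under the 25% v 50% assumption, against a standard error of about 4.8. It is about 0.8 to 2.3 points under 15% v 30%. It would be perhaps half or less if baseline risk status is measured on the same individuals.

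The documents do not show that the arms differ in age or sex, that the trial's estimates are biased, or that any sample-size figure is wrong. Nor would adjustment for age and sex cure differential recruitment, since clinicians may also have selected on characteristics that were not measured.

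**What to change.** Enter the young person's age (a spline, or 14–17 v 18–24) and, where recorded, sex as fixed covariates in all young-person-level models for detection, risk behaviour and distress, whether or not they look imbalanced. Report the model without them as a sensitivity analysis. State that this reduces but does not remove differential-recruitment bias. In the same place, say on whom and when baseline risk factor status is measured.

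The article says that analysis is already underway. Unless the change is made before arm-level results are seen, label it a late addition.

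The cost is a short addition to the analysis plan and two or three individual-level model terms. No practice-level degrees of freedom are lost and no stated sample size changes. Age is needed for eligibility; the availability of sex should be confirmed.

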### **Economic evaluation**

The economic evaluation will be undertaken from a health care perspective. Costs include the resource use required to develop and administer the intervention, changes in clinical practice associated with the initial GP or PN consultation and the young person’s subsequent health service utilisation during the follow-up period. Health outcomes consist of the changes in risky behaviours measured in the main trial and health related quality of life using the SF-12 [66]. The incremental costs will be compared to the incremental benefits in a cost consequence analysis. If the intervention proves to be effective at reducing specific risk behaviours then a cost-effectiveness analysis will also be reported. Finally, if the intervention is successful in improving quality of life (as reflected in the SF-12 data and the associated SF-6D quality of life tariffs), then a cost-utility analysis will also be reported [67].

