### **Addressing the evidence gap in health risk screening and early intervention in primary care**

We designed a pragmatic cluster randomised trial [48] to assess acceptability, effectiveness and economic efficiency of a universal, opportunistic, psychosocial health risk screening and motivational interviewing intervention for young people presenting to primary care. The motivational interviewing intervention was designed to train clinicians to respond to young people’s health risk behaviours in a non-judgemental way while still encouraging young people to contemplate change or adopt changes that would reduce health risks. We also designed a nested feasibility study to examine the role of nurses in screening and counselling youth. Additionally we explored the role of nurses in providing a point of linkage between the practice and other service providers who might collaborate in a care plan for youth issues requiring multidisciplinary input. We believe that this is the first ever trial to address these issues.

In this paper, we describe the development and piloting of the intervention and the protocol for the cluster randomised trial as well as variations in the implementation of the trial since trial registration. The detailed protocol for the economic evaluation and practice nurse feasibility study will be discussed in later outcome papers.

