### **Study questions**

The primary aims of the trial are to compare the intervention and comparison arms on: 

1. Clinicians’ accuracy in identifying risk-taking behaviour;

2. Young people’s uptake of risky behaviour or intention to change or reduction of established behaviour at three and 12 months post-intervention; and

3. Acceptability of risk screening to young people, their parents and practice staff.

The secondary aims include comparing both study arms on: 

1. Young people’s pathways to care, trust in their clinician and likelihood of returning for future visits;

2. Parents’ attitudes toward the concept of a youth friendly practice policy including seeing the clinician alone and conditional confidentiality.

The main study hypotheses originally reported in our trial registration [49] were that: 

1) An opportunistic screening tool for health risk in youth will improve the clinician’s detection by 25% compared to interview alone;

2) Specific risk response training, including motivational interviewing, will result in at least 10% overall less uptake of risky behaviour or greater intention to change or reduction in established risk behaviour three months post-intervention compared to usual care;

3) Any reduction in health risks would be sustained to 12 months;

4) The benefits for youth and society as a whole will outweigh the costs of the intervention; and

5) Youth preventive care and linkage role will be acceptable to PNs and general practice staff and will be feasible to implement.

We made three amendments to the hypotheses to overcome practical barriers to conducting the trial. The amendment to our first hypothesis, about the screening tool alone improving clinician detection, was made prior to patient recruitment, during the intervention phase of the trial. All intervention practices were given the screening tool and mentored in how they might integrate it with their office systems. However each practice differed in the way they used it (or whether they used it at all). Some preferred to use the desk top mnemonic chart we also provided to prompt screening. We therefore required flexibility in the way we implemented practice change, a characteristic of pragmatic trials [48]. Our first hypothesis was hence redefined to test whether the intervention training *and* screening tools will improve clinician detection.

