The second amendment, made soon after recruitment of patients had begun, was to change the absolute percentage effect size shown in hypothesis one and two, to 31% and 15%, respectively. The minimum detectable effect sizes were modified in response to the slow recruitment rate of young people because the original sample size required to detect smaller effect sizes was unattainable within the time frame and resources available to conduct the study (see section on sample size estimates).

Hypothesis four, about the intent to conduct an economic analysis from a societal perspective, was amended during the study pilot to instead conduct the economic analysis from a health care perspective only. The societal evaluation approach requires the estimation of a monetary valuation of benefits. In addition to the large sample sizes required for such an analysis, there would have been a considerable responder burden as young people would already have been surveyed with a long interview for the main health outcomes.

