#### ***Sample size estimation***

Sample size calculations assumed 80% power at a significance level of 5% for two- sided test and an intra-clinic correlation of 0.04 [63]. The original first hypothesis was based on the assumption that 40% of youth attending general practice have health risk behaviours or emotional distress, and that trained GPs, at best, will pick up 60% with interview alone [17], equivalent to 24% of all presenting youth. For a clinically meaningful outcome, we expected the clinicians to detect a further 25% of youth with risk taking behaviours using the screening tool with the interview (intervention arm), equivalent to an additional 10% of all presenting youth to the practice, compared to the comparison arm. To detect a 10% difference in the clinician’s detection of risk taking behaviours of all youth attending general practice between the two study arms, 1760 youth (44 per practice in 40 practices) were required after allowing for a variance inflation factor (VIF) of 2.72.

To allow for the slow recruitment rates, we revised our intended intervention effect in the clinician’s detection of risk taking behaviours of all youth attending general practice from 10% to 12.5% (equivalent to intervention clinicians picking up a further 31% of youth with risk taking behaviours instead of the 25% originally proposed). This small adjustment to the effect size reduced the required sample size to a total of 720 youth (18 per practice in 40 practices with a VIF of 1.68). To allow for a 40% loss to follow-up of youth over 12 months [64], we calculated that a total of 30 youth in each practice needed to be interviewed at recruitment. An additional two practices were also recruited to allow for loss of practices during follow-up.

The revised sample size also affects the difference in the prevalence of the risk behaviours that can be detected between the study arms in the second hypothesis. Table 2 gives the minimal effect size that can be detected in the prevalence of selected risk behaviours between the study arms at 3 and 12 months follow-up (power 80%, alpha 5% for a two-sided test) for the revised sample size for a range of intra-cluster correlations. The revised sample size is sufficient to detect at least a 15% difference between the two study arms for each of the risk behaviours with 80% power and alpha at 5% for a two-sided test.

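### Cost-effectiveness and cost-utility analyses are reported only after a favourable effect, so a null, imprecise or adverse result gives neither, and the ratios that do appear tend to be optimistic

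*Protocol article*

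**What the plan says.** The Economic evaluation section describes three analyses.

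- **Cost-consequence analysis, no condition attached:** "The incremental costs will be compared to the incremental benefits in a cost consequence analysis".
- **Cost-effectiveness analysis, conditional:** "If the intervention proves to be effective at reducing specific risk behaviours then a cost-effectiveness analysis will also be reported". The behaviours are not named and no criterion for being effective is given.
- **Cost-utility analysis, conditional:** "if the intervention is successful in improving quality of life (as reflected in the SF-12 data and the associated SF-6D quality of life tariffs"). Again no criterion is given.

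Hypothesis 4, as registered, reads "The benefits for youth and society as a whole will outweigh the costs of the intervention" (Study questions). The same section says that it was "amended during the study pilot to instead conduct the economic analysis from a health care perspective only". The amended form is the one that the economic evaluation has to serve.

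The Background defers the economic detail: "The detailed protocol for the economic evaluation and practice nurse feasibility study will be discussed in later outcome papers".

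**The concern.** An economic evaluation estimates incremental cost and incremental effect together, with the uncertainty in both. A non-significant effect is not a zero effect. When the effect is small or imprecise, a reader still needs to know how likely the intervention is to be good value. Making the two ratio-based analyses depend on a favourable effect does two things.

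1. **Gaps after an unfavourable result.** If quality of life is unchanged, poorly estimated or worse, no cost per QALY and no statement of its uncertainty is produced. The same applies to each behaviour that does not succeed. The article makes economic efficiency a trial aim and says that evidence on the cost-effectiveness of screening is scarce. Under this rule a null trial would leave much of that gap open.
2. **Selection on the estimate.** A ratio is shown only when the effect estimate was large enough to count as success. On average such estimates exceed the true effect, so cost per unit of effect looks lower than it is.

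**Working it through.** The article gives no figure for the economic evaluation itself. The sample size fixes the precision of the behaviour effects that trigger the cost-effectiveness analysis, so I reproduced it first.

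**Inputs (Sample size estimation and Table 2).** "Sample size calculations assumed 80% power at a significance level of 5% for two- sided test and an intra-clinic correlation of 0.04". The comparison-arm detection rate is 24% and the revised difference 12.5 points, so 36.5% in the intervention arm. There are 18 youth in each of 40 practices, 720 in all. Comparison-arm alcohol prevalence is 41% and tobacco 24%.

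**Step 1: the plan's own figures.**
- Variance inflation: 1 + (18 − 1) × 0.04 = 1.68, as stated.
- Two proportions, 24% v 36.5%, pooled test, no continuity correction: 211 per arm. Then 2 × 211 × 1.68 = 709, against the stated 720 (within 3%; power at 720 is 80.6%).
- Table 2, alcohol, detectable reduction at correlations 0.01, 0.04 and 0.07: 10.8, 12.9 and 14.6 points, against the stated 11, 13 and 15.

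The design figures reproduce, so they can be used for the next step.

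**Step 2: what the filter does to one behaviour.** Assumption: being effective means a favourable two-sided p<0.05 on that behaviour.

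- Effective number per arm: 360 / 1.68 = 214.
- For prevalence p and true reduction d: SE = √{[p(1 − p) + (p − d)(1 − p + d)] / 214}.
- The estimate must exceed c = 1.96 × SE. With a = (c − d) / SE, the chance of reporting is 1 − Φ(a), and the mean reported effect is d + SE × φ(a) / [1 − Φ(a)].

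Worked case: alcohol, p = 0.41, d = 0.10.
- SE = 0.0461, c = 0.0904, a = −0.208.
- Chance of reporting = 0.582.
- Mean reported effect = 0.10 + 0.0461 × 0.390 / 0.582 = 0.131, which is 1.31 times the truth.

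| True reduction, alcohol (points) | Chance of reporting | Mean reported effect (points) | Inflation | Cost per unit of effect relative to truth |
|---|---|---|---|---|
| 0 | 2.5% | 11.1 | – | – |
| 5 | 18% | 11.8 | 2.35 | 0.42 |
| 8 | 41% | 12.4 | 1.56 | 0.64 |
| 10 | 58% | 13.1 | 1.31 | 0.76 |
| 13 | 81% | 14.5 | 1.11 | 0.90 |
| 15 | 92% | 15.8 | 1.05 | 0.95 |

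The last column holds cost fixed and divides by the mean reported effect. For tobacco (24%) the inflation is about 2.0 at 5 points, 1.15 at 10 and 1.03 at 13.

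**Step 3: without the conditions.** The chance of reporting becomes 100% and the selection factor 1.0. Sample size and alpha are unchanged.

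**The case against.** **The cost-consequence analysis is unconditional.** This is the strongest point on the other side, and it stands. A reader might infer that a null trial gives no economic answer at all, or that what remains does not set benefit against cost. The article says that incremental costs will be compared with incremental benefits in any case. What goes missing is the ratio, the cost per QALY and their joint uncertainty.

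**Hypothesis 4 can still be answered unfavourably.** A reader might infer that only a favourable answer is possible. That does not follow. With no benefit, the cost-consequence analysis would show costs without gain. With benefit, the ratio may still be poor, because the condition is on effect and not on cost. The plan should also be judged against the amended hypothesis and not the registered societal wording.

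**The unselected effects remain visible.** The Data analysis plan promises intervention effect estimates with 95% confidence intervals and p-values, with no success condition. A careful reader can set these beside any ratio. This softens the harm, but does not supply the missing joint uncertainty.

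**The inflation rests on an assumed trigger and is small at design effects.** This also stands. At the 13 to 15 points that Table 2 gives as detectable for alcohol at correlations of 0.04 and 0.07, the inflation is about 1.05 to 1.1. The larger factors need smaller true effects, which the article neither states nor rules out.

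**Economic detail is deferred to later papers.** The deferral excuses the missing criterion and the absence of methods such as a bootstrap or acceptability curves. It does not undo a reporting rule that this article states outright.

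**Conclusion.** The concern holds in a limited form. Two of the three economic analyses are reported only after a favourable effect. A null, imprecise or adverse result would therefore leave amended hypothesis 4 with a cost-consequence comparison, but without a cost-effectiveness or cost-utility estimate and its joint uncertainty. That much follows from the text and needs no assumption.

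The optimism in any ratio that is reported is a tendency, and its size depends on the true effect: minor where the trial is well powered, about 1.3-fold at 10 points and 2.4-fold at 5 points for alcohol. These figures assume a p<0.05 trigger, a single behaviour, 720 youth analysed, a correlation of 0.04, a normal approximation and fixed cost. They do not cover selection across several behaviours or the quality-of-life condition.

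**What to change.** Delete both conditions in the Economic evaluation section. State that the following will be reported whatever the clinical result:

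- incremental cost, incremental SF-6D QALYs and the cost-utility result;
- cost-effectiveness for risk behaviours named in advance;
- joint cost-effect uncertainty for each, by a method that respects clustering by practice.

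The choice of method can stay with the later economic paper. The Discussion says that analysis is already under way, so the behaviours should be named before their results are used to choose them; if that is no longer possible, the paper should say so.

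The cost is a change of wording and modest extra analysis. Table 1 shows that health service use, risk behaviours and SF-12 are collected at the exit and follow-up interviews whatever the result, so no new data are needed. The drawback is that some intervals may be wide, but that width is itself information for policy readers.
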